## 1.9 Secondary Imaging Core Lab (ICL)

The objective of the second ICL is to make a final ruling a) in case there is a disagreement in the clinical rating and the first core-lab rating of the MDCT or b) in case the majority of the first core-lab ratings (at least 5 out of 6) of the FDCT is hemorrhage positive and the ground truth is hemorrhage negative, to determine if the hemorrhage has occurred between both scans. The second ICL will be blinded to the rating of the core-lab 1 but not to the remaining clinical data. The second ICL defines the ground truth for all patients in whom the clinical rating and the rating of core-lab 1 of the MDCT are divergent (majority vote).

The second ICL will be performed by [name], MD (Head of the Clinic for diagnostic and interventional Neuroradiology, University Hospital Bern), who is an internationally known Neuroradiologist with more than 20 years of experience in the assessment of cranial non-contrast images in stroke patients. All readings will be done in accordance with a core-lab manual, which will be written prior to any assessment. As the second ICL will not be blinded to any data (except to the readings of the first ICL), it is not a problem that [name], MD might have been involved in the original enrollment of patients at the study site Inselspital Bern, Bern, Switzerland.

[name], MD

Head of the Clinic for diagnostical and interventional Neuroradiology

University Hospital Bern

[name]

[name]

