- Bucket 2 and 3 (haemorrhage patients) 126 patients including 14 patients in bucket 3 (isolated infratentorial or basal intracranial haemorrhage including perimesencephalic SAH)

Local investigators must keep a screening log.

The primary objective (sensitivity and specificity of non-contrast syngo DynaCT Sine Spin imaging for the detection of intracranial haemorrhage) will be assessed by blinded readers in an imaging core-lab. All readers will be blinded to all clinical characteristics and will not be involved in the treatment or enrolment of patients. Prior to the core-lab assessment all scans will be anonymized, reconstructed in a standardised way (fixed angles and slide sizes) and randomized. All readings will be noted on standardized forms.

The ground truth (i.e., if an intracranial haemorrhage is present or not) will be defined based only on the MDCT scans according to the following procedure: If the reading of the clinical reader (the enrolling physician at the participating site) and the reader from the first blinded core-lab (provided by the Neurovascular Imaging Research Core, [name], University of California LA, Los Angeles, California, USA) is consistent this will be deemed as ground truth. If they are inconsistent a second core-lab (provided by [name], Inselspital Bern, Bern, Switzerland) will make a final ruling (majority vote). The second core-lab can use all available clinical information but will be blinded to the results of the reading from core lab one. The following table illustrates the definition of the ground truth:

| Modality | Reader | Analysis |
| --- | --- | --- |
| MDCT | Clinical Reader | Agreement: ground truth |
|  | Core-Lab 1 | Disagreement: Unblinded expert reader in 2^nd^ corelab determines ground truth (majority vote) |

Table 1: Definition of the ground truth

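### The second core-lab adjudicator may have enrolled and read the patient being adjudicated, so the MDCT majority vote can count one person's view twice

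*Protocol*

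**What the plan says.** The ground truth is built from the MDCT. Section 6.1 names the first vote as that of "the clinical reader (the enrolling physician at the participating site". The second vote is the blinded MDCT reader of the first core lab. If the two agree, that is the truth. The second core lab, which is one neuroradiologist, is called "in case there is a disagreement in the clinical rating and the first core-lab rating of the MDCT". Section 1.9 then gives that person the final word: "The second ICL defines the ground truth for all patients in whom the clinical rating and the rating of core-lab 1" diverge, and it labels the result a majority vote.

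On masking, section 1.9 states: "The second ICL will be blinded to the rating of the core-lab 1 but not to the remaining clinical data". On overlap of roles, it accepts that the adjudicator "might have been involved in the original enrollment of patients at the study site" where the adjudicator works, and reasons: "As the second ICL will not be blinded to any data (except to the readings of the first ICL), it is not a problem".

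The same person has a second task (sections 1.9, 6.1 and 9.2). When at least 5 of 6 FDCT readers call a hemorrhage and the ground truth is negative, the adjudicator decides whether the bleed arose between the scans. If so, the patient leaves the analysis.

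The Synopsis (Measurements and procedures) describes the second core lab as independent. The protocol contains no recusal rule, no alternate adjudicator, and no requirement that the adjudicator differ from the clinical reader.

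**The concern.** A majority of three protects against error only if the three views are separate. Section 1.9 treats the overlap as a question of what the adjudicator may see. The issue is whether the adjudicator has already committed to an answer. The Synopsis requires the investigator to enter at enrolment whether the stroke is hemorrhagic, and where, so a physician who enrols a patient has put a view on record before any adjudication.

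The protocol is stricter with others. First core-lab readers may not enrol or treat patients (sections 6.1 and 6.2), DSMC members may not enrol (section 1.7), and the MDCT reader may not be one of the FDCT readers. The person with the last word on truth is the exception.

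The reference standard decides which patients count towards sensitivity and which towards specificity. The between-scan ruling decides whether a near-unanimous false positive stays in specificity.

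**Working it through.** No figure in the protocol needs reproducing here. The check is mainly of roles, with arithmetic for scale.

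**1. Who casts which vote.**
- Vote 1: the clinical reader, who is the enrolling physician (6.1).
- Vote 2: the first core lab, blinded (6.1).
- Vote 3: the adjudicator, only if votes 1 and 2 differ (1.9).
- Overlap allowed: the adjudicator may have been involved in enrolment at one site (1.9).

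Taken together, votes 1 and 3 can belong to the same person for some patients at that site.

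**2. Does masking to the first core lab help?** The rating is yes or no, and an MDCT referral happens only on disagreement. An adjudicator who made the clinical reading therefore knows that the first core lab said the opposite. Any adjudicator shown the clinical reading could infer the same.

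**3. What separate votes are worth (illustration).** The protocol gives no MDCT error rate, so assume an error rate e per reader, with independent errors.
- Three different readers: error = 3e² − 2e³.
- Adjudicator is the clinical reader and repeats the reading: error = e² + e(1 − e) = e.

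| e | three readers | same person repeats |
|---|---|---|
| 1% | 0.03% | 1% |
| 2% | 0.12% | 2% |
| 5% | 0.73% | 5% |

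The last column is no better than one reader alone. It applies only to patients the adjudicator read, and only if the first view is repeated.

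**4. How many patients.** Assume the site enrols 5 to 15% of 252 and 2 to 5% of MDCT pairs disagree.
- Low: 252 × 0.05 × 0.02 = 0.25.
- High: 252 × 0.15 × 0.05 = 1.9.
- Equal shares over the maximum of 30 sites: 252/30 = 8.4 patients (3.3%), giving 8.4 × 0.02 = 0.17 to 8.4 × 0.05 = 0.42.

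These are all discordant patients at the site, in both groups together. Those personally enrolled and read by the adjudicator are a subset.

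**5. Weight of one patient.** There are 238/2 = 119 patients per group after drop-out. If all six readings of a hemorrhage-negative patient change status, specificity moves by about 1/119 = 0.84 points. The 14 isolated infratentorial cases share a total weight of 2%, so one of them moves sensitivity by about 0.02/14 = 0.14 points. A change of ground truth also moves the patient between denominators.

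**6. Closeness to the margin.** With one reading per patient and n = 119, the exact (Clopper-Pearson) lower 95% limits are 96.95% with 0 errors, 95.41% with 1 and 94.06% with 2. This is not the trial's rule. At the assumed specificity of 98%, the chance of at most one error is 0.98^119 + 119 × 0.02 × 0.98^118 = about 31%, whereas section 11.2 states 90% power for a six-reader mixed model.

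**The case against.** The adjudicator reads the scan afresh, with all clinical data and under a manual written beforehand, and may reverse the earlier view. This stands. A reader might infer that the first core lab can never prevail for these patients; the protocol does not support that. The risk is anchoring, and the last column of the table overstates the error to the extent that the adjudicator corrects it on re-reading.

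Section 1.9 says only that the adjudicator might have been involved in enrolment. It does not say that the adjudicator made the clinical reading, and a recusal rule could sit in the core-lab manual, which is not at hand. This also stands, so the point is about what the protocol permits. Section 6.1 nevertheless equates the two roles, and section 1.9 dismisses the overlap where it could have restricted it.

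A reader might set the one-error limit beside the upper estimate of 1.9 patients and conclude that the overlap could decide the trial. That does not follow. The limit belongs to a different analysis, the patient count spans both groups and is a site-wide upper bound on assumed rates, and no direction of bias is known.

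The between-scan ruling is not a vote. One unblinded person makes it for every patient by design, so the overlap adds no second vote there. What remains is an independence concern for the adjudicator's own patients.

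**Conclusion.** The point holds as a gap in independence at one site. Sections 1.9 and 6.1 together let one person supply two of the three views that define the truth for a discordant MDCT. In such a case the first core lab prevails only if the adjudicator overturns their own reading. The justification in section 1.9 does not address this, and the Synopsis description of that core lab as independent conflicts with it.

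The size is small. Only patients whom the adjudicator personally enrolled and who reach adjudication are affected. The protocol gives no count, and the range of 0.25 to 1.9 rests on assumed site shares and disagreement rates. The change is worth making because it is cheap and protects the reference standard.

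**What to change.** Replace the sentence in section 1.9 that accepts the overlap with: *The second core-lab adjudicator does not act as enrolling physician or clinical reader for any trial patient.* Other physicians at that site take these roles. Section 1.9 and the Synopsis then agree.

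For patients whom the adjudicator has already enrolled or read, report how many reached adjudication. Repeat the primary analysis with the blinded first core-lab MDCT reading as their ground truth, and retain any of them excluded under the between-scan rule.

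The cost is one sentence, a rota constraint at one site, and one sensitivity analysis on readings already collected. One physician can no longer enrol there. If the change counts as substantial, section 2.10 requires ethics approval. This version is dated April 2024, with first patient-in anticipated for October 2022 and last patient-out for December 2024. If enrolment is nearly complete, the sensitivity analysis is the effective part.

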# 2. ETHICAL AND REGULATORY ASPECTS

We acknowledge the ethical requirements in clinical research as they were outlined by Emanuel E et al.^21^ As most of the points are detailed in later parts of this clinical investigation plan (CIP), we will give in this section only a shortened statement with regard to the points (1) value of the research, (2) scientific validity, (3) fair subject selection, (4) favorable risk-benefit ratio, (5) independent review, (6) informed consent and (7) respect for the enrolled subject.

The value of the proposed clinical investigation lies in the validation of a new imaging modality for suspected acute stroke patients, which might allow in the future to triage severely affected stroke patients faster (studies point to a time gain of approximately 30 minutes).^11-13^ This might ultimately lead to better clinical outcomes in this often severely affected patient group, which would lower their burden of disease substantially.^9, 14, 22-25^ As stroke is still one of the leading causes of mortality and disability worldwide,^26-28^ this could have relevant effects on socioeconomic costs as well.^29^ (see section 3.1) The proposed clinical investigation will be the first investigation evaluating the non-contrast syngo DynaCT Sine Spin imaging protocol for the detection of acute, spontaneously occurring intracranial hemorrhage prospectively and with blinded outcome assessment, guaranteeing high validity of the findings. Furthermore, patients will be enrolled based mainly on clinical features (i.e., their symptoms), guaranteeing that the population enrolled within this clinical investigation, resembles the patient population which undergoes the procedure in everyday practice. The syngo DynaCT Sine Spin scan will be done as in standard clinical practice. This guarantees high external validity of our findings (see section 6). As pointed out subject selection will be done in close accordance with the patient population, which would undergo this procedure in everyday clinical practice (see section 7). Treatment delays due to the syngo DynaCT Sine Spin will be negligible, as the patient positioning on the angiography table is identical for the syngo DynaCT Sine Spin as for the following intervention. Therefore, the net treatment delay in patients not routinely undergoing syngo DynaCT Sine Spin is below 1 minute (time for acquisition of the sine spin FDCT is 7 seconds). In most of the subjects the second syngo DynaCT Sine Spin is clinical routine as it is often used to obtain a baseline status of the subject after transport to the angiography suite. This is done for example to rule out new or worsening hemorrhages prior to the intervention. In some subjects presenting with an intraparenchymal/intraventricular hemorrhagethe syngo DynaCT Sine Spin scan is not usually done in clinical routine. These subjects will receive minor extra radiation (up to 2.5 mSV) as in these patients the syngo DynaCT Sine Spin would not be done in clinical routine. ^6^

However, for evaluating bleeding detection it is of pivotal importance to include all kinds of bleedings to provide an evidence-based judgement on the diagnostic performance for the detection of intracranial hemorrhage. Although the subjects will have no personal gain from participating in this investigation, the gain for the society might be considerable due to improved triage of stroke patients (see section 3.7). The CIP will be independently reviewed by the ECs of all participating sites and an independent data safety monitoring committee (DSMC) will oversee the trial conduct. Informed consent must be obtained in all subjects in accordance with local legislation and standards (see section 2.7). Furthermore, prior to performing non-contrast syngo DynaCT Sine Spin the local investigator must obtain agreement from the treating physician to perform non-contrast syngo DynaCT Sine Spin in the subject at question. All subjects will be informed about the clinical investigation and have the right to withdraw from it at any point without giving any reason. This will not affect their treatment. In case of new information becoming available, which affects the subjects in any way, it will be promptly communicated to them through the local investigators.

Before the trial will be started, the protocol, the proposed patient information and consent form as well as other trial-specific documents will be submitted to a properly constituted Ethics Committee (EC) / Internal Review Board (IRB) in agreement with local legal requirements, for formal approval. Any amendment to the protocol will as well be approved (if legally required) by these institutions. The decision of the EC/IRB concerning the conduct of the trial will be made in writing to the Sponsor-Investigators before commencement of this trial. At each site the clinical trial can only begin once approval from all required authorities (for the site) has been received. Any additional requirements imposed by the authorities shall be implemented.

## 2.1 Registration of the investigation

The investigation is registered on clincialtrials.gov (NCT05458908). In addition, we will register the trial in national language on the SNCTP (via BASEC) platform.

## 2.2 Categorization of the investigation (Switzerland)

According to Swiss legislation (Human research act (HRA)^1^ and Art 6 Clinical Trial Ordinance-MD (ClinO-MD)^2, 4^) the clinical investigation is categorized as a clinical investigation concerning a medical device class A2, since the medical device under investigation is CE-certified in accordance with Art 13 MedDO, commercially available in Switzerland and it will be used within its intended use. Since the performance of the non-contrast syngo DynaCT Sine Spin is in a subgroup of the enrolled patients not clinical routine, and associated with minor excess radiation (up to 2.5 mSv according to internal measurements and recent publications)^6^, the clinical investigation is rated as A2.^4^ No contrast media will be applied due to the study.*See Appendix C- US Protocol Amendments

## 2.3 Competent Ethics Committee (CEC)

In Switzerland, the protocol will be submitted according to Swiss law and according to the procedures of Swissethics. EC approvals for foreign sites will be obtained by the responsible PIs according to country specific applicable law with the support of the CTU in Basel. The responsible PI at each site will ensure that approval from an appropriately constituted EC is sought for the clinical trial. No changes will be made to the protocol without prior Sponsor-Investigators and EC approval, except where necessary to eliminate apparent immediate hazards to patients.

The US chair is responsible for the adherence to all applicable national regulations and requirements including EC and institutional review board (IRB) approval in North America.

*See Appendix C- US Protocol Amendments

### 2.3.1 Reporting duties to the Competent Ethics Committee

Amendments are reported according to Art. 15 ClinO-MD (see also 2.10). No changes are made to the CIP without prior Sponsor and CEC approval, except where necessary to eliminate immediate hazards to subjects. Refer to chapter 10 for safety reporting.

The regular or premature end of the investigation as well as the interruption of the investigation is reported to the CEC within 15 days (within 24 hours if it is due to security reasons) (Art. 36 ClinO-MD). The reasons for a premature end or an interruption have to be explained.

A final report shall be submitted within one year after the regular end of the investigation and within 3 months after a premature end of the investigation (Art. 37 ClinO-MD).

The US chair is responsible for timely reporting to the CEC and IRB in the USA.

## 2.4 Competent Authorities (CA)

The MD used in this trial is commercially available and consequently conformity labelled. They will be used in accordance with the approved indications and instructions. Therefore, no approval from the Swiss competent authority Swissmedic is needed.

For sites in the USA and EU, approval will be obtained according to local requirements (if applicable). For the US this is the responsibility of the US Chair.

## 2.5 Ethical Conduct of the Trial

The investigation will be carried out according to the CIP and with principles enunciated in the current

version of the Declaration of Helsinki^30^, the European Regulation on medical devices 2017/745 (MDR)^31^, the Norms ISO14155, the ICH-guidelines of Good Clinical Practice (GCP)^32^ as applicable, the Swiss Human Research Act (HRA)^1^ and its Ordinances and Swiss regulatory authority’s requirements. The CEC and the CA will receive the Annual Safety Report (ASR) and interim reports and be notified about investigation stop/end in agreement with local requirements.

Sites abroad will be informed about trial stop/end in the same manner as ECs in Switzerland and will receive annual safety and interim reports for submission to their ECs. Abroad, the local PI is responsible for the adherence to all applicable national and local requirements.

The US chair will be informed about trial stop/end in the same manner as ECs in Switzerland and sites abroad and will receive annual safety and interim reports for submission to their ECs. In the USA the US chair is responsible for the adherence to all applicable national and local requirements.

## 2.6 Declaration of interest

The trial is funded by Siemens Healthineers AG. This is an academic investigator-initiated trial (IIT). Experts nominated by and employees of Siemens Healthineers AG were consulted during the protocol development, but the Sponsor-Investigator and the Co-PI had the final decisions to all suggestions. Siemens Healthineers AG will have no influence on data acquisition, data management, data analyses or scientific interpretation and publication of the results.

## 2.7 Patient Information and Informed Consent

Each institution must follow their institutional and national EC policy as well as local IRB policy (if applicable) for obtaining informed consent. All information sheets and consent forms will be submitted to the EC to be reviewed and approved. Legally correct consenting procedures must be guaranteed for every subject.

This clinical investigation will include mainly vulnerable patients in an emergency situation. All patients must have a severe stroke or symptoms suggestive of an intracranial bleeding. Most patients need an emergency treatment. As determined by the inclusion criteria, only patients with severe neurological deficits (National Institute of Health Stroke Scale (NIHSS) ≥ 7) or symptoms suggestive of an intracranial bleeding are eligible for this clinical investigation. Some of these patients may not be able to give informed consent. There is no alternative group of patients in whom this procedure could be studied, as we must ensure that it is studied in a comparable patient population to which it will be applied in the future. Otherwise, our results would have no external validity. Because we include mainly vulnerable patients in an emergency and due to the life-threatening situation, no delay to the enrolment procedure can be accepted. In patients capable of giving informed consent, informed consent must be obtained prior to enrollment of the patient. The enrolling physician will decide after consultation with the treating neurologist/neurosurgeon if the patient is able to give informed consent. If he/she is not able to give informed consent due to the severity of his neurological deficit and there is no declaration of intent available (i.e., advance directive) that he does not want to participate in clinical research, the patient will be included in the trial without prior informed consent by him-/herself or a next of kin/legally authorized representative (LAR) and recovery consent from the patients or his/her next of kin/LAR has to be obtained post-hoc. An independent physician will be consulted prior to enrolling the patient into the trial to ensure and confirm that the enrollment of the patient does not cause any harm or poses an excess risk to the patient. This will be documented on a specific form. The independent physician will also ensure, that there were no signs or symptoms present, suggesting the unwillingness of the patient to participate in this clinical investigation.

In all patients, who were enrolled without prior informed consent by him-/herself, the patient or their LAR/next of kin will be sought for consent at the earliest time post-procedure. If a subject is not capable of giving their informed consent, all reasonable efforts will be made to obtain informed consent from the subject’s legally authorized representative (for example, relative or caregiver). This includes cases where the subject dies during the procedure or shortly thereafter or when the severity of the subject’s condition prohibits them from providing informed consent.

The local investigator explains (either before enrollment if possible or at the earliest time post-procedure) to each subject or in case the subject is not capable of giving informed consent to their LAR/next of kin the nature of the investigation, its purpose, the procedures involved, the expected duration, the potential risks and benefits and any discomfort it may entail. Each subject or their LAR/next of kin is informed that the participation in the investigation is voluntary and that he/she may withdraw from the investigation at any time and that withdrawal of consent will not affect the subject`s subsequent medical assistance and treatment. The subjects or their LAR/next of kin are informed that he/she can ask any question, and consult with family members, friends, their treating physicians, or other experts before deciding about their participation in the investigation. Enough time is given to the subjects or if applicable their LAR/Next of kin. The subjects or their LAR/next of kin are informed that authorized individuals other than their treating physician may examine his/her medical records. All subjects or their LAR/next of kin are given a subject information sheet and a consent form describing the investigation and providing sufficient information for the subjects or their LAR/next of kin to make an informed decision about their participation in the investigation.

Please refer to Appendix Patient Information and Informed Consent for detailed information regarding the inclusion requirements and informed consent process.

*See Appendix C- US Protocol Amendments

